**PART 2: IMPLEMENTER IN-DEPTH INTERVIEW (3)**

**Domains, topic questions, and probes:** Use the table below to help you administer the questions during the interview.

| Domain                               | Topic and Probes                                                                                                                                      |
|--------------------------------------|-------------------------------------------------------------------------------------------------------------------------------------------------------|
| 4. Training                   | Where you directly involved with the training components of the HFI?
If no, skip to Question 4.                                             |
|                                      | a) Can you describe the training sessions that you had with the participants? Probe: what happened in the training?                            |
|                                      | b) What do you think worked particularly well in the training, which will ensure that the participants will take home specific messages?              |
|                                      | c) What impact do you think this training will have on the practices of participants in reality?                                                      |
|                                      | d) What do you think can be strengthened in the training to enable health workers to really change their practice?                                    |
| 5. Uptake of the intervention | a) Aside from the training components, can you comment on whether the information and management tools provided were able to be taken up in practice? |
|                                      | b) What are the enabling factors to using this new knowledge in practice?                                                                             |
|                                      | c) In your opinion, what things limit translation of this new knowledge into practice?                                                                |
| 6. Motivation towards job     | a) We want to know how we could do this programme elsewhere. What skills and characteristics do you think are needed to do your job really well?      |

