#### **4.5.1. Assessment of hypothesised impacts**

Some impacts may be hypothesised in advance based on the predicted and potential mechanisms of change resulting from the intervention as described under 'intended effects' in the logic model (Figure 4.2). Both quantitative and qualitative methods will be used to assess these impacts. For quantitative measurements, existing data collection methods used in ACT PRIME will be utilized wherever possible including cross-sectional survey questionnaires, cohort household surveys, patient exit interviews, health worker knowledge questionnaires, and health facility surveillance questionnaires.

For qualitative assessments of intended effects, IDIs and FGDs will be used to assess whether and how the intervention affected specific hypothesised impacts. IDIs will be conducted with implementers and health workers in the HFI arm, and FGDs will be conducted with primary caregivers.

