## 5 STUDY PROCEDURES

### 5.1. OVERVIEW

The ACT PROCESS study proposed here will be implemented in parallel with the ACT PRIME study, but will be carried out by a different team of field researchers. Self-filled questionnaires, health worker communication assessments and patient exit interviews, IDIs and semi-structured questionnaires, FGDs, and a contextual record will be used to evaluate the process, context and impact of the HFI in the ACT PRIME study. The self-filled questionnaires will be used to evaluate the HFI training and will be conducted during the HFI roll-out period in March-May 2011. The health worker communication assessments and patient exit interviews will be conducted immediately before and after the HFI training in patient-centered services, and then approximately six months following the training for a total of three cycles. The IDIs and semi-structured questionnaires, and FGDs will be conducted approximately 9-12 months after the HFI roll-out. The structured contextual record will be completed by the study team at three-monthly intervals. The timelines for the process, context and impact evaluations in relation to ACT PRIME are outlined in the study procedures timeline below.

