## **5.6. IN-DEPTH INTERVIEWS**

We plan to conduct IDIs with HFI implementers, health workers from the HFI arm and key stakeholders. The purpose of the IDIs is to collect information on the contextual factors and perceptions of the HFI as it is being implemented as well as the expected and unexpected impacts of the HFI. Written informed consent to conduct the IDI will be obtained from all participants before beginning (Appendix P) as outlined in section 8.2. The IDIs with health workers and implementers will be conducted approximately 9-12 months after the HFI roll-out. The IDIs with key stakeholders will be conducted approximately one year after the HFI roll-out.

Implementer participants for the IDIs will be purposively selected from the ACT PRIME implementation team. Any implementers who delivered health worker training, worked on drug distribution to health centers, or had significant interaction with health workers or district or local officials during the HFI implementation or follow-up period will be invited to participate. We plan to complete up to five IDIs with implementers, following the pre-defined topic guide (Appendix Q).

Health workers from the HFI arm will be selected by convenience sampling. We plan to complete up to 10 IDIs with health workers stationed at HFI health centers, following the pre-defined topic guide (Appendix R).

Key stakeholders will be purposively selected based on their involvement with the ACT PRIME study during the HFI implementation period or their role in the health system. For example, we plan to interview stakeholders involved with drug distribution and staffing for the HFI, district officials including the District Health Officer and Deputy District Health Officer, as well as key staff from the Tororo sub-district and sub-county level. We expect to complete up to ten IDIs with key stakeholders, following the pre-defined topic guide (Appendix S).

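### The implementer interview guide has no direct question, put to every implementer, on what changed because of the HFI: its one explicit impact item is a forecast, about training only, behind a trainer-only gate

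*Supplement*

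**What the plan says.** Table 4.1 marks the implementer interviews for process, context and impact, with a maximum of 5. Section 4.5.1 names them among the qualitative sources on hypothesised impacts: "IDIs will be conducted with implementers and health workers in the HFI arm, and FGDs will be conducted with primary caregivers". Section 5.6 gives expected and unexpected impacts as part of their purpose and sets the timing: "The IDIs with health workers and implementers will be conducted approximately 9-12 months after the HFI roll-out". It invites not only trainers but also anyone who "worked on drug distribution to health centers, or had significant interaction with health workers or district or local officials", and it says the interviews follow the topic guide in Appendix Q.

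Section 4.5.2 adds that most-significant-change questions come first in the focus groups and in-depth interviews, which then turn to hypothesised impacts directly.

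In Appendix Q, domain 4 (Training) begins with a filter: "Where you directly involved with the training components of the HFI". The instruction after it reads "If no, skip to Question 4". Item 4b asks what worked well in the training, "which will ensure that the participants will take home specific messages". Item 4c is the impact question: "What impact do you think this training will have on the practices of participants in reality".

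**The concern.** The guide does not match the job the protocol gives it. By the time of the interview, implementers have watched several months of practice across the HFI health centers. The only question that names impact asks them to predict instead of report, and about one component of four. Section 4.3 lists the aspects under evaluation as training, management tools, supply of AL and RDTs, and interaction with the district. Staff recruited for their supply or liaison work are the natural witnesses on the last two, yet they are routed away from that question.

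At stake is one marked cell of the impact evaluation. A forecast from the people who delivered a programme is weak evidence of what it did. If the guide is followed, direct accounts of observed change depend on an incidental answer or on the interviewer improvising.

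**Working it through.** No sample size or error rate is involved. The check is a count of items, a date calculation and a comparison of guides.

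**1. Items in Appendix Q** (filter question not counted)

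| Domain | Items | Asked of | Bearing on impact |
|---|---|---|---|
| 1 Role | 1 | all | none |
| 2 Participants' expectations | 2 | all | probe to 2b asks what else happened that participants had not expected |
| 3 Implementation | 5 | all | delivery as planned; most and least successful components |
| 4 Training | 4 | trainers (intended) | 4c: impact of training, future tense |
| 5 Uptake | 3 | all | 5a: whether tools were taken up in practice |
| 6 Skills needed | 1 | all | none |
| 7 Context | 3 | all | other programmes and influences |
| 8 Closing | 1 | all | open |

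Total: 1 + 2 + 5 + 4 + 3 + 1 + 3 + 1 = 20. One of the 20 names impact (4c). Without domain 4, 20 - 4 = 16 remain, and none of these names impact. That is a count by wording: the probe to 2b and item 5a touch on consequences and uptake without asking what the HFI changed.

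**2. Timing.** Section 5.1 says the training questionnaires "will be conducted during the HFI roll-out period in March-May 2011".
- Earliest interview: start of March 2011 + 9 months = start of December 2011.
- Latest interview: end of May 2011 + 12 months = end of May 2012.
- Shortest gap since training: end of May 2011 to start of December 2011 = 6 months.
- Longest gap: start of March 2011 to end of May 2012 = 15 months.

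The future tense in 4b and 4c is out of date anywhere in that range.

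**3. Routing.** The filter sits inside domain 4 and sends those who answer no to Question 4, the block it should bypass. The next domain is 5, so the intended target is evidently Question 5. Read literally, the skip returns non-trainers to the training questions. Read as intended, it takes them past 4c.

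**4. Most-significant-change questions.** Appendix Q has none. The health worker guide (Appendix R, domain 2), the stakeholder guide (Appendix S, domain 2) and both focus group guides have them, though not always as the opening item. The rule in 4.5.2 can be read as limited to interviews that go on to hypothesised impacts. Section 4.5.1 puts the implementer interviews in that group, so the rule reaches them on either reading.

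**5. Tense in a parallel guide.** The training item in the health worker guide (domain 3a) asks retrospectively how the training has affected the respondent's work. The implementer guide is the one that differs.

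**The case against.** The strongest reply is that the guide does gather retrospective material. A reader who sees only 4c might infer that these interviews would yield expectations and nothing observed. The documents do not support that: the probe to 2b invites unexpected consequences, which is one of the stated purposes, and 5a asks about actual uptake of tools. Both are put to supply and liaison staff as well as trainers. If use of the tools is an intended effect in the logic model, 5a is itself an impact item. Figure 4.2 is not shown, so this cannot be settled here.

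Three other strong readings also fail.
- The tense might suggest a guide written for the day of the training. The guide does not say so, and items such as 3d and 3e look back two years. Only 4b and 4c are clearly out of time.
- It might seem that the interviews could not help explain why the HFI worked or not. Domains 3, 5 and 7 ask exactly about delivery, enablers, limits and outside influences.
- It might seem that impact evidence as a whole is compromised. Implementers supply at most 5 of 25 in-depth interviews, and health workers, stakeholders, caregivers and community health workers are all asked about change.

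It is also fair that this is a topic guide, so a good interviewer can shift the tense. The contact summary form asks about problems with the guide after each interview. That is a late safeguard with at most five interviews, and section 5.6 states no piloting of this guide, whereas 5.7 does for the questionnaires.

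What remains is that 2b is framed by participants' expectations, 5a by tools other than training, and domain 3 by delivery. None of them asks what changed in practice or care as a result of the HFI.

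**Conclusion.** The point holds in a limited form. The implementer interviews are a stated source on expected and unexpected impacts, but the only explicit impact question is a forecast, concerns training alone and is meant for trainers alone. The skip beside it is misdirected, and the most-significant-change questions that the protocol calls for are absent. Some retrospective information would still come from every implementer. What is lacking is a direct question, put to all of them, on what the HFI changed.

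The scope is up to 5 interviews and one cell of Table 4.1. No comparison between arms depends on it. The conclusion assumes that the guide is followed broadly as printed and that the skip is meant to lead to Question 5. It is worth acting on because it changes what is collected, and it cannot be repaired once the interviews are done.

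**What to change.** In Appendix Q:
1. Open the guide with the most-significant-change questions, as section 4.5.2 provides.
2. Put 4b and 4c in the past tense. For 4c, for example: What changes in health workers' practice have you seen since the training, at which health centers, and what did you see?
3. Outside the training filter, ask every implementer one past-tense question on the observed effects of the component they delivered (training, management tools, supply, or contact with the district).
4. Correct the skip to Question 5.

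The cost is a short edit to one appendix and a few extra minutes in at most five interviews. No other instrument, sample or analysis changes.

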**PART 2: IMPLEMENTER IN-DEPTH INTERVIEW (4)**

**Domains, topic questions, and probes:** Use the table below to help you administer the questions during the interview.

| Domain                                                                              | Topic and Probes                                                                                                                                                           |
|--------------------------------------------------------------------------------------------|-----------------------------------------------------------------------------------------------------------------------------------------------------------------------------------|
| 7. Context                                                                          | a) Aside from the HFI, can you describe any other programmes/interventions involving malaria in the area? Probe: is the programme at the community or health centre level? |
|                                                                                            | b) Aside from the HFI, can you describe any other health-related programmes/interventions in the area? Probe: is the programme at the community or health centre level?    |
|                                                                                            | c) Are there any other factors you think may have influenced the delivery or receipt of the ACT PRIME HFI?                                                                        |
| 8. Closing                                                                          | Is there anything else you think is important about the implementation of the HFI intervention that we have not talked about?                                                     |
| 
 
✓ Summarise
 
✓ Thank participant
 
 |                                                                                                                                                                                   |

**PART 3: CONTACT SUMMARY FORM (1)**

Complete this form after the interview.

**Study ID**

[ ] [ ]

**Date**

[ ] [ ] / [ ] [ ] / [ ] [ ]  
day month year

1. How would you describe the atmosphere and context of the interview (*Include interview location and how this may have affected responses*)?

2. What were the main points made by the respondent during this interview?

**PART 3: CONTACT SUMMARY FORM (2)**

**Study ID**

[ ] [ ]

**Date**

[ ] [ ] / [ ] [ ] / [ ] [ ]  
day month year

3. What new information did you gain through this interview compared to previous interviews?

4. Was there anything surprising to you personally? Or that made you think differently?

5. What messages did you take from this interview to improve the intervention design?

6. Were there any problems with the topic guide (e.g. wording, order of topics, missing topics) you experienced in this interview?

## APPENDIX R: IDI DATA COLLECTION TOOL

### HEALTH WORKERS (HFI)

| Health centre code | Study ID | Date                                          |
|--------------------|----------|-----------------------------------------------|
| [ ] [ ]            | [ ] [ ]  | [ ] [ ] / [ ] [ ] / [ ] [ ]
day month year |

**Position:**

|                             |                      |                             |                          |
|-----------------------------|----------------------|-----------------------------|--------------------------|
| 1 = In-charge               | 5 = Clinical officer | 9 = Public health nurse     | 13 = Health assistant    |
| 2 = Senior medical officer  | 6 = Nursing officer  | 10 = Nursing aide/assistant | 14 = Health educator     |
| 3 = Medical officer         | 7 = Enrolled nurse   | 11 = Laboratory technician  | 15 = Volunteer           |
| 4 = Senior clinical officer | 8 = Midwife          | 12 = Laboratory assistant   | 15 = Other _____ [ ] [ ] |

### DEMOGRAPHIC INFORMATION

|                                                                                                                                                                                                                               |                                                                                                                                                                                                                                                                                                                                                                                                                                                                                       |          |             |                       |                       |                         |                 |                 |                        |                  |         |
|-------------------------------------------------------------------------------------------------------------------------------------------------------------------------------------------------------------------------------|---------------------------------------------------------------------------------------------------------------------------------------------------------------------------------------------------------------------------------------------------------------------------------------------------------------------------------------------------------------------------------------------------------------------------------------------------------------------------------------|----------|-------------|-----------------------|-----------------------|-------------------------|-----------------|-----------------|------------------------|------------------|---------|
| 
1. Age Years [ ] [ ]
 
2. Gender 1 = Male [ ]
2 = Female [ ]
 
3. Originally from this area? 1 = Yes [ ]
2 = No [ ]
 
4. Number of years worked in this job [ ] [ ]
 | 
5. Highest level of education or qualification achieved
 
 
 0 = None	4 = Diploma	
 
 1 = Primary (P1 — P7)	5 = Bachelor's degree	
 
 2 = Secondary (S1 — S6)	88 = Don't know	
 
 3 = Certificate	99 = Refused to answer	
 
 77 = Other _____	[ ] [ ]	
 
 
6. Year graduated [ ] [ ] [ ] [ ]
 | 0 = None | 4 = Diploma | 1 = Primary (P1 — P7) | 5 = Bachelor's degree | 2 = Secondary (S1 — S6) | 88 = Don't know | 3 = Certificate | 99 = Refused to answer | 77 = Other _____ | [ ] [ ] |
| 0 = None                                                                                                                                                                                                                      | 4 = Diploma                                                                                                                                                                                                                                                                                                                                                                                                                                                                           |          |             |                       |                       |                         |                 |                 |                        |                  |         |
| 1 = Primary (P1 — P7)                                                                                                                                                                                                         | 5 = Bachelor's degree                                                                                                                                                                                                                                                                                                                                                                                                                                                                 |          |             |                       |                       |                         |                 |                 |                        |                  |         |
| 2 = Secondary (S1 — S6)                                                                                                                                                                                                       | 88 = Don't know                                                                                                                                                                                                                                                                                                                                                                                                                                                                       |          |             |                       |                       |                         |                 |                 |                        |                  |         |
| 3 = Certificate                                                                                                                                                                                                               | 99 = Refused to answer                                                                                                                                                                                                                                                                                                                                                                                                                                                                |          |             |                       |                       |                         |                 |                 |                        |                  |         |
| 77 = Other _____                                                                                                                                                                                                              | [ ] [ ]                                                                                                                                                                                                                                                                                                                                                                                                                                                                               |          |             |                       |                       |                         |                 |                 |                        |                  |         |

